### Sample size

#### Primary outcome in Phase A

The sample size for the primary outcome in Phase A was calculated based on the Minimally Important Difference (MID) of the EQ-5D-5L derived utility scores among lung cancer patients in the United States of America (USA). The index-based score is typically interpreted along a continuum where 1 represents full health and 0 represents dead, with some health states being worse than dead (<0). A MID of 0.07 and SD of 0.16 is considered clinically significant for this patient population [13]. The MID of 0.07 was considered clinically significant for this patient population because in 2007, Pickard et al. had reported that for EQ-5D utility scores in the USA, MIDs, grouped by performance status, ranged from 0.07 to 0.09 for all cancers and for lung cancer, but when based on FACT-G quintiles, MIDs were 0.06 to 0.07 in all cancers, and 0.05 to 0.06 in lung cancer [13]. A sample size of 166 patients, with 83 patients per arm will ensure detection of this difference with 80% power at a level of significance of 0.05. A 10% drop out rate was used to account for those potential withdrawals, therefore a total of 186 participants will be recruited to the trial, 93 participants per trial arm.

#### Secondary outcome in Phase B

Differences in QALY will require a higher number of measurements to be detected. Overall survival at 5-years will also require a larger sample size over a longer period of observation. These secondary outcomes of interest require the trial to be repowered so that they can be adequately powered. Based on a hypothesized 10% 5-year survival difference between the control arm and the experimental arm, the estimated sample sizes for two-sample comparison of survivor functions using the Log-rank test Freedman method with 80% power at a level of significance of 0.05 is 592 patients, with 296 patients per arm. A drop-out rate is not factored into this analysis since the Freedman method of censoring was employed, accounting for loss of patients over time. Also, an assumption for Stage I patients was made during this sample size calculation, since the majority of patients who are operated on are Stage I. Also, this calculation is not a non-inferiority design. This larger, sufficient sample size will allow comparison of difference in overall cost-effectiveness and survival.

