### Eligibility criteria

#### Participants

Participants are eligible to participate in the trial if they sign the Patient Information and Informed Consent Form (PICF) and meet the following eligibility criteria:

*Inclusion criteria*:

Age ≥ 18 yearsClinical stage I, II or IIIa non-small cell lung cancer (NSCLC)Candidates for minimally invasive pulmonary lobectomy, as determined by the operating surgeon.

*Exclusion criteria*:

Patients who received neoadjuvant treatmentClinical stage IIIb or IV NSCLCNot a candidate for minimally invasive lobectomy

During the COVID-19 pandemic, participants will be eligible to participate in the trial if they meet the eligibility criteria and provide either written or verbal consent.

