### Plans to promote participant retention and complete follow-up

Participants will be informed that they are free to withdraw from the trial at any time, without fear of any negative repercussions. Investigators may also withdraw participants from the trial (e.g., to protect the participants’ safety). All trial withdrawals will be documented by date and reason for withdrawal. If the participant chooses to withdraw prior to randomization, their data will be excluded from the trial. If a participant chooses to withdraw after randomization, their data will be included, unless otherwise requested.

There is minimal anticipated loss to follow-up, as the majority of the interval data (3 weeks, 12 weeks, 6 months, 18 months, 1, 2, 3, 4 and 5 years) will be collected at the same time that the participant has their standard scheduled post-surgery follow-up visit in clinic. The availability of a trial coordinator will ensure that the Trial Health Questionnaire is completed at each of these follow-up clinic visits. If a participant misses a follow-up visit, it will be considered a deviation from the protocol, but the participant will remain in the trial and all attempts to contact the participant to conduct the visit over the telephone will be made, even if the visit occurs late. Major deviations from the protocol will be documented (e.g., the nature of the deviation and rationale for the deviation) and the REB will be notified as per requirements.

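### The Phase B size of 592 contains no allowance for loss to follow-up: the Freedman method does not supply one, so the stated 80% power needs complete 5-year vital status

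*Protocol article*

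**What the plan says.** The Protocol article, under Secondary outcome in Phase B, sets the effect first: "Based on a hypothesized 10% 5-year survival difference between the control arm and the experimental arm". The resulting size is given as "Log-rank test Freedman method with 80% power at a level of significance of 0.05 is 592 patients, with 296 patients per arm". The same paragraph then explains why no allowance for loss was added: "A drop-out rate is not factored into this analysis since the Freedman method of censoring was employed, accounting for loss of patients over time". On the survival rate assumed, it says only that "an assumption for Stage I patients was made during this sample size calculation, since the majority of patients who are operated on are Stage I". It prints no control survival rate, hazard ratio, number of deaths or loss rate.

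Three other places bear on this:

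- Primary outcome in Phase A treats drop-out explicitly: "A 10% drop out rate was used to account for those potential withdrawals".
- Plans to promote participant retention and complete follow-up states, without a figure: "There is minimal anticipated loss to follow-up".
- The eligibility criteria under Participants admit "stage I, II or IIIa non-small cell lung cancer".

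**The concern.** The sentence confuses two things. The log-rank test handles censored patients validly, so loss unrelated to prognosis does not bias the comparison. But power depends on the number of deaths observed, and a patient lost before 5 years may take a death with them. Freedman's conversion from deaths to patients divides by the average probability of dying by 5 years. That divisor covers administrative censoring, meaning patients alive when follow-up ends. It does not cover earlier loss.

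Adequate power for survival is one of the article's stated reasons for extending the trial to Phase B. If the 80% holds only when every patient's 5-year status is known, the article should say so. Otherwise a reader will take the figure as already protected against loss when judging a survival result that shows no difference.

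**Working it through.** **Inputs from the Protocol article:** absolute difference in 5-year survival of 10 percentage points; Freedman log-rank method; 80% power; significance level 0.05 (taken as two-sided, since sidedness is not stated); 1:1 allocation; no drop-out rate entered; N = 592.

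**Inputs assumed here:** control survival, which is inferred below, and loss rates of 5%, 10% and 20%. The 10% is the Phase A rate, used only for scale.

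**Step 1. Reproduce 592.** With survival S1 (control) and S2:

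- HR = ln(S2)/ln(S1)
- deaths d = (1.96 + 0.8416)² × ((1 + HR)/(1 − HR))²
- N = 2d/(2 − S1 − S2)

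At S1 = 0.70 and S2 = 0.80:

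- HR = ln 0.80/ln 0.70 = 0.6256
- (1 + HR)/(1 − HR) = 4.342
- d = 7.849 × 4.342² = 147.99
- N = 2 × 147.99/0.50 = 591.95, that is 592, or 296 per arm

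This is the printed figure with zero loss. With a 10-point difference and zero loss, the only other solution is near 25% versus 35%, which does not fit a stage I assumption.

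**Step 2. What this match proves.** By itself it does not prove that loss was set to zero, because zero loss was imposed in solving for the rates. For example, 72% versus 82% needs 129 deaths, and with 5% loss N = (2 × 129/0.46)/0.95 = 590.4, which also rounds up to 296 per arm. The zero-loss reading rests on the article's own statement that no drop-out rate was factored in; the 70%/80% match agrees with it.

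**Step 3. Power at 592 with loss, on 70% versus 80%.** Power = Φ(√d × (1 − HR)/(1 + HR) − 1.96). Two patterns bracket the effect:

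- *All loss at the start:* d = 148 × (1 − w).
- *Loss spread evenly (constant drop-out rate):* with cumulative hazards L = −ln S and G = −ln(1 − w), the probability that a death is observed is L/(L + G) × (1 − S(1 − w)). For w = 10% this is 0.2856 (control) and 0.1902 (robotic), mean 0.2379, so d = 592 × 0.2379 = 140.8.

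| Loss by 5 years | Evenly spread: deaths, power | All at start: deaths, power |
|---|---|---|
| 0% | 148, 80.0% | 148, 80.0% |
| 5% | 144, 79.0% | 141, 78.0% |
| 10% | 141, 78.0% | 133, 75.7% |
| 20% | 133, 75.8% | 118, 70.7% |

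For scale only, holding 80% at 10% loss would take about 622 patients (147.99/0.2379) to 658 (592/0.9).

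**Step 4. Sensitivity to the stage I assumption, no loss, N = 592.** The direction depends on which effect measure is held fixed.

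- *10-point difference held, 65% versus 75%:* HR = 0.668; required deaths 198; expected deaths 296 × (0.35 + 0.25) = 177.6; power 75.6%. At 60% and 55% control survival, power is 72.5% and 70.5%.
- *HR 0.6256 held, control 65%:* robotic survival 0.65^0.6256 = 76.4%; expected deaths 296 × (0.350 + 0.236) = 173.5; power 85.9%. At 60% and 55%, power is 90.2% and 93.3%.

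**The case against.** The strongest reply is that loss of survival status may be very small. The article expects minimal loss, keeps patients who miss visits in the trial and pursues them by telephone, and takes 5-year status from a chart review. A missed questionnaire is therefore not a lost survival outcome, and the 10% used in Phase A concerns a 12-week questionnaire endpoint. The all-at-start figures are a worst case; with evenly spread loss, power is 79.0% at 5% and 78.0% at 10%. All of this stands and limits the size of the problem. It does not rescue the stated reason, because the sample-size paragraph relies on the Freedman method and not on expected minimal loss. The chart review also draws on the surgeon's surveillance notes, so a patient no longer seen there may have no recorded status.

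A reader might go further and infer that 80% power is not delivered in the stage I to IIIa population enrolled. The documents do not support that. The article discloses that "an assumption for Stage I patients was made during this sample size calculation" and gives a reason. It gives no stage mix and no stage-specific survival, and Step 4 shows that lower control survival can move power either way.

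A reader might also treat 70%, 80% and 148 deaths as the sponsor's inputs. They are back-calculated and unconfirmed.

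**Conclusion.** The point holds in a limited form. The claim that the Freedman method accounts for loss of patients is incorrect, whatever survival rates were used. By the article's own account 592 carries no loss allowance, so the stated 80% power requires complete 5-year vital status. The size of the shortfall depends on the inferred 70% versus 80% and on assumed loss rates: about 1 to 2 percentage points at 5% loss, 2 to 4 at 10%, and 4 to 9 at 20%. Severity is moderate, since overall survival is a secondary outcome and the shortfall at modest loss is small.

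The gap between the stage I assumption and the wider eligibility merits a sensitivity statement only. Nor can 148 deaths serve as a universal benchmark: at 65% versus 75%, about 178 deaths would be expected, more than 148, yet power is 75.6% because that smaller relative effect requires 198.

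**What to change.** - Delete the statement that the Freedman method accounts for loss over time.
- Have the sponsor state the control survival rate, hazard ratio, required deaths and loss rate actually used. The 70%, 80% and 148 derived here are for the sponsor to confirm or correct, not to adopt.
- Restate the power of 592 patients with an explicit loss allowance, as a range if the loss rate is uncertain. If 70% versus 80% is confirmed, the table in the working supplies the figures.
- Add one sentence on the stage I assumption, saying how power changes at lower control survival both with the 10-point difference held and with the hazard ratio held.
- When the survival result is reported, compare observed deaths with the event target for the effect assumed, not with a fixed 148.

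The cost is a change of wording and a slightly less favourable stated power. No added enrolment is needed, and because Phase B is still recruiting, the correction can be made before the survival analysis.

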### Recruitment

Historical institutional volumes at both Canadian centers demonstrate a total of 8–10 RTS-Lobectomies and 10–12 VATS-Lobectomies performed each month. A relatively high recruitment rate (~70–80%) is expected, due to public enthusiasm towards robotic surgery in Canada. The estimated completion of accrual is within 15 years of the trial start date.

## Assignment of interventions: Allocation

### Sequence generation

A statistician who is a member of the Biostatistics Unit at St. Joseph’s Healthcare Hamilton, generated the randomization sequence using SAS [14]. Randomization was stratified by surgeon. For each surgeon, a unique randomization sequence using the random permuted-block design (with blocks of varying sizes) to randomize patients in a 1:1 ratio to one of two intervention arms, VATS-Lobectomy or RTS-Lobectomy, was generated. This method ensures that an approximately equal number of patients will be allocated to each treatment group.

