#### Surgeons

The trial may be subject to performance bias, based on surgeon preference. To mitigate this, only surgeons who have demonstrated proficiency by independent completion of more than 30 VATS- and 30 RTS-Lobectomies [11] will be able to recruit participants for the trial.

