## Statistical methods

### Statistical methods for primary and secondary outcomes

Baseline characteristics of both treatment groups will be compared to ensure homogeneity in the patient population. Descriptive statistics will be reported by treatment group where categorical variables will be reported as counts (percentages) and continuous variables as mean (standard deviation) or as median (25^th^ percentile, 75th percentile). All analyses of primary and secondary outcomes will be carried out based on the intention-to-treat principle. Unadjusted comparisons of continuous outcome measures will be carried out using an independent t-test or the Wilcoxon rank-sum test if the assumptions of the t-test were violated. Unadjusted comparisons of categorical outcome measures will be computed using the chi-squared test, or the Fisher’s exact test if any of the expected values in the contingency table is less than 5, or McNemar’s test. For adjusted analyses, multivariable logistic regression analyses will be used for binary outcomes and multivariable linear regression for continuous outcomes. The results of comparisons between groups will be presented as mean differences for continuous outcomes and relative risks or odds ratios for binary outcomes, with corresponding 95% confidence intervals and associated p-values. ANOVA will be used for repeated measures. Survival will be compared using the Kaplan-Meier method and cox proportional hazard models. Survival curves will be compared using the Log-rank test. P-values will be reported to three decimal places with p-values less than 0.001 reported as p < 0.001. All analyses will be performed using SAS. Table 3 provides a summary of the variables, measures and methods of analysis.

**Table 3 pone.0261767.t003:** Variables, measures and methods of analysis.

Variable/Outcome	Hypothesis*	Outcome	Method of Analysis

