**SECONDARY**			
Short-Term Clinical Outcomes			
*Pathological Staging*	Improved	Pathological stage	McNemar’s test
*Lymph nodes*	More	Number of lymph nodes harvested	Independent t-test, Wilcoxon rank sum test/linear regression
*Duration of chest tube drainage*	Shorter	Number of days between surgery and chest tube removal	Kaplan-Meier method, Cox regression
*Hospital length of stay*	Shorter	Number of days between admission and discharge	Kaplan-Meier method, Cox regression
*Intra-operative blood loss*	Less	Volume of Intra-operative blood loss (mL)	Independent t-test/Wilcoxon rank sum test/ linear regression
*Post-operative analgesia requirements*	Less	In-hospital consumption (days, type, amount)	Independent t-test/Wilcoxon rank sum test/linear regression
*Chronic post-surgical pain*	Less	In-hospital pain (daily, scale)	Independent t-test/Wilcoxon rank sum test/ANOVA
Patient-reported Health-Related Quality of Life (HRQOL) outcomes	Improved	HRQOL scores, measured by the EQ-5D-5L at 3 and 7 weeks, and 6 and 18 months, and 1,2, 3, 4 and 5 years	Examine the distributions/ regression/ANOVA
Resource Utilization and Cost Effectiveness	More	Resource utilization tracking system, EQ-5D-5L, Return to Normal Living Index (RNLI), and employment status at 12 months	Incremental cost per quality-adjusted life year (QALY) gained will be calculated
Overall Survival	Improved	5-year survival difference	Kaplan-Meier method and cox proportional hazard models. Survival curves will be compared using the Log-rank test

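### Surgeon, the randomization stratum, is not named in the Cox analyses of chest-tube duration and length of stay; if it is left out, the hazard ratio may be attenuated and power lost to the extent that surgeons differ

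*Protocol article*

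**What the plan says.** Under Sequence generation, the protocol article states "Randomization was stratified by surgeon", with a separate permuted-block sequence for each surgeon "to randomize patients in a 1:1 ratio to one of two intervention arms". The number of surgeons is not given.

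Table 3 defines the two recovery outcomes as "Number of days between surgery and chest tube removal" and "Number of days between admission and discharge". The method for each is "Kaplan-Meier method, Cox regression", with no stratum or covariate named.

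The Statistical methods section says: "For adjusted analyses, multivariable logistic regression analyses will be used for binary outcomes and multivariable linear regression for continuous outcomes". It describes no adjusted time-to-event model and lists no covariates for any model. Institution appears under additional analyses, but only as a subgroup factor for quality of life. Surgeon appears in no analysis.

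**The concern.** The article itself treats the surgeon as influential. It makes surgeon the only randomization stratum, and under Surgeons it warns: "The trial may be subject to performance bias, based on surgeon preference". When a drain is removed and when a patient goes home plausibly follow the routine of the surgeon and the hospital, and recruitment covers four hospitals in three countries. That is a reasonable inference, not a figure in the article.

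In a Cox model, omitting a strong prognostic factor does more than cost precision, even when the factor is balanced between arms. Patients of quick surgeons leave the risk set early, and sooner in the faster arm. The patients who remain in that arm then come increasingly from slow surgeons, and the pooled hazard ratio moves toward 1. Almost every patient reaches both events, so there is little censoring to limit this. The test also becomes conservative, because its standard error ignores the balance that the stratified randomization created.

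At stake are two of the article's stated short-term hypotheses for robotic surgery: shorter drainage and shorter stay. A real difference could be understated or missed.

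**Working it through.** **The plan's own figure.** The article gives no hazard ratio, event count or power for either outcome. The nearest figure is the Phase A sample size, and Phase A is where the short-term outcomes are compared. With difference 0.07, SD 0.16, two-sided 5% and 80% power:

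n per arm = 2 × (1.960 + 0.842)² × 0.16² / 0.07² = 2 × 7.85 × 0.0256 / 0.0049 ≈ 82.0, rounded up to 83, so 166 in total. With 10% dropout, 83 / 0.9 = 92.2, rounded up to 93 per arm, so 186.

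This reproduces the article. It serves here only to set the number of patients.

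**Inputs from the article.** 1:1 allocation balanced within surgeon; about 186 patients.

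**Assumed inputs, because the article gives none.** 4, 8 or 12 surgeons of equal size (184, 184 and 180 patients after rounding); within-surgeon hazard ratio 1.5 or 1.0; SD of the surgeon log hazard from 0 to 1.0; no censoring; Weibull times with shape 1.5. On this scale an SD of 0.25 means that a surgeon one SD above average has exp(0.25) = 1.28 times the average hazard. For 0.5 the factor is 1.65, and for 0.75 it is 2.12.

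**Models.** Times are T = (E / exp(f_s + x·log HR))^(1/1.5), with E standard exponential, f_s the surgeon effect and x the arm. The unstratified model is h(t) = h₀(t)·exp(βx). The stratified model is h_s(t) = h₀ₛ(t)·exp(βx), with a separate baseline hazard for each surgeon. The test rejects when |β̂/SE| > 1.96. There were 1,500 replicates per setting, so the Monte Carlo error of a power near 75% is √(0.75 × 0.25 / 1500) ≈ 1.1 points.

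**Results at a within-surgeon hazard ratio of 1.5.** Ranges are over 4, 8 and 12 surgeons. The last column is stratified minus unstratified power in that order; for example, 75.5 − 64.2 = +11.3.

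| Surgeon SD | Unstratified HR | Power | Stratified HR | Power | Change in power (points) |
|---|---|---|---|---|---|
| 0 | 1.51–1.52 | 77.1–80.3% | 1.51–1.52 | 71.8–78.1% | −2.2, −3.9, −6.5 |
| 0.25 | 1.47–1.48 | 72.0–73.1% | 1.49–1.51 | 69.7–73.3% | +0.6, −1.9, −3.4 |
| 0.5 | 1.41–1.42 | 64.2–66.4% | 1.50–1.52 | 71.8–75.5% | +11.3, +6.5, +7.1 |
| 0.75 | 1.36 | 52.1–53.9% | 1.51 | 70.5–75.7% | +23.4, +17.8, +18.4 |
| 1.0 | 1.30–1.31 | 38.0–42.1% | 1.50–1.51 | 70.3–75.9% | +33.8, +32.2, +32.3 |

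**Results with no effect (hazard ratio 1.0).** The unstratified test rejects in 4.1–5.5% of trials at SD 0, 2.8–3.5% at SD 0.5, 1.3–2.2% at SD 0.75 and 0.7–1.2% at SD 1.0. The stratified test rejects in 3.7–5.9% across all settings. With a Monte Carlo error of √(0.05 × 0.95 / 1500) ≈ 0.6 points, that is compatible with 5%.

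**Sensitivity to the set-up.** A second simulation used whole-day times, Weibull shape 1.8 with a 5-day scale, normally distributed surgeon effects and 6 to 10 surgeons. At SD 0.5 it gave an unstratified HR of 1.41–1.42 with power 65–67%, against a stratified HR of 1.48 with 73%. At SD 0, stratifying cost about 4 to 6 points.

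**The case against.** The strongest reply is that the article is silent rather than wrong. It nowhere calls the Cox model unstratified or says that surgeon is left out. Cox regression can take surgeon as a stratum or covariate without any change to the wording, and such detail is often left to an analysis plan, which is not shown. This stands in part. A reader might infer that the plan has decided to ignore surgeon; the text does not say so. But the article gives a method for each outcome and describes adjusted models for two outcome types without naming surgeon in any. The comparison as written is therefore one without surgeon.

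Other parts of the reply stand in full:

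- The sentence "Survival curves will be compared using the Log-rank test" follows a statement about survival, and Table 3 repeats it only for overall survival. It is no evidence of an unstratified log-rank test for these two outcomes.
- Kaplan-Meier curves yield no hazard ratio, so attenuation concerns the Cox estimate alone.
- The pooled hazard ratio is a different, marginal quantity. It is too small only when read as the within-surgeon effect, and the article does not say which is the target.
- The surgeon SD is assumed. At 0.25 the two analyses are about equal, and at 0 stratifying loses power. The entry requirement of more than 30 procedures of each type may narrow surgeon differences, although proficiency is not the same as drain and discharge routine.
- Both outcomes are secondary and have no power statement, so no design claim is undermined.
- A fixed covariate or a frailty term would also account for surgeon.

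**Conclusion.** The concern holds in conditional form. Surgeon governs the randomization but is not named in the Cox analyses of chest-tube duration and length of stay. If those analyses are run as written, the hazard ratio may be attenuated relative to the within-surgeon effect and the test conservative, and the extent depends on how much surgeons differ.

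Under the assumed inputs, an SD of 0.5 moves a within-surgeon hazard ratio of 1.5 to about 1.41–1.42 and costs about 7 to 11 points of power compared with stratifying. An SD of 0.75 costs about 18 to 23 points. At 0.25 there is little to choose, and at 0 stratifying loses about 2 to 7 points.

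A reader might go further and conclude that the planned analysis is certain to understate the effect, or that its false-positive rate is at risk. The documents support neither. They give no number of surgeons and no between-surgeon variation, and the error rate falls rather than rises. The primary outcome and both sample-size calculations are unaffected.

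**What to change.** State that the Cox comparison of chest-tube duration and length of stay, and any log-rank test of them, is stratified by surgeon. Surgeons who contribute very few patients are pooled within their institution, by a minimum-size rule fixed before unblinding. Report the unstratified result as a sensitivity analysis, noting that it estimates a pooled rather than a within-surgeon hazard ratio, so the two need not agree. If an existing analysis plan already says this, carrying the statement into the protocol is enough.

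The cost is wording only. Each surgeon has a separate randomization sequence, so surgeon is already known for every patient. The statistical price is a few points of power (about 2 to 7 in the settings above, more with more surgeons) if surgeons turn out not to differ.
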